**Procedure**

*Recruitment*

Recruitment for the study will be done through an ad posted on Alcohol Help [(www.alkoholhjalpen.se).](https://translate.google.com/translate?hl=sv&prev=_t&sl=sv&tl=en&u=http://www.alkoholhjalpen.se/) If recruitment in this way proves to be slow, ads on the Internet will be used. The advertisement informs that there is a study on the treatment of alcohol problems currently taking place and that there is the opportunity to participate. Those who show interest in participating must take part of the informed consent (see Appendix 4 .1) and specify gender and age, and fill in the AUDIT - form. If the inclusion criteria for age and / or hazardous use of alcohol is not met, the individual will be informed that the hazardous use of alcohol is not present in the answers, and that he / she therefore does not belong to the target group of the study (Annex 4.1. 1 .1). If the inclusion criteria are met, the participant receives information on this and creates a user account (Annex 4.1.1.2). Then the other questionnaires will be answered (see above under Materials). The randomization to the three study arms is fully automated. Participants may then immediately access the group via their own user account (Annex 4.1. 2-4). Participants will get access to a new module every week during the first 7 weeks. Then there is a break in treatment for three weeks. Then the participants get access to a finishing module. After completion of treatment, participants fill in outcome measurements again and processing issues and follow-up questions (Annexes 5.1-5.10).

*Treatment*

Participants in Group 1 who choose to have therapist support through chat, will receive this 40 minutes / week at a predetermined time. Chat for one will be in a private "chat room," on the treatment site they have access to through the personal user account. Participants in Group 1 who choose contact via messages, as well as participants in Group 2 will have access to therapist support through written messages once a week. The messages will be available through the treatment site. Participants will receive regular e-mail messages when messages from the therapist are posted on the treatment site. Participants in Group 3 will work on their own, without therapist support during treatment. These, however, if necessary, will be able to ask questions of the research team.

Participants in all groups will have a reminder sent to them via regular e-mail once a week when the new module is available, when messages are available, reminders of time for chat, for relevance, and so on. In case of no contact, reminders via email will be sent. Should the participant's mood considerably worsen during treatment so that the he or she cannot or should not continue treatment, they will be offered personal contact with a licensed therapist from the research group for communication about a health care contact that can suit the participant's current needs. All e-therapists have at least basic training in psychotherapy. During the course of treatment continuous internal supervision will be held once a week at the beginning of the study and then at least once every two weeks to discuss experiences and knowledge.

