**Materials**

*The treatment program TO*

The treatment used in this study is a Swedish translation of a Dutch program that has shown very good outcomes in a randomized controlled study, where the program was compared to a self-help variation without therapist support (Blankers et al., 2011). The program contains eight modules focusing on relapse prevention (Saxon & Wirbing, 2004).

*Figure 1.* Three-arm pilot study of Internet-based treatment for problematic alcohol use with and without dealing with support

*Outcome Measure*

AUDIT (Alcohol Use Disorders Identification Test) (Annex 5.1)   is a well established and widely used instrument for assessing alcohol consumption (Bergman & Källmén, 2002; Saunders, Aasland, Babor, De La Fuente, & Grant, 1993). It consists of 10 questions answered 0-4 with a final score between 0 and 40. The result is then divided into hazardous use, abuse and dependence. Limit the risk of abuse required for men at 8 points or more, for women at 6 points or more. There is also a short version of the instrument, the AUDIT-C ("consumption"), which contains only the first three questions and is used to map the current situation. On some occasions it may be expedient to use one single query to get a picture of someone's drinking. For these cases, question 3 concerning high episodic drinking is the one that is best correlated with the total score (Berman, Wennberg, & Källmén, 2012).

 DUDIT (Drug Use Disorders Identification Test) (Appendix 5.2)   is a questionnaire designed to find out drug consumption and drug-related problems of various kinds.   The test consists of 11 questions that are scored between 0 and 4, giving a final score of 44 points. The result of the test is divided into hazardous use, abuse and dependence. The test has been shown to identify problematic use in studies. As for the AUDIT, there is a shorter version of DUDIT, DUDIT C, where only the first four questions dealing with consumption included. This version of the test, however, is unfortunately not enough studied. What you can infer is that the limit of 1 point for hazardous use applies to both DUDIT C as well as for DUDIT. (Berman, Bergman, Palmstierna, & Schlyter, 2005; Berman et al., 2012).

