**Participants**

A total of 80 people seeking help via the Internet will be recruited (see below for the recruitment procedure). All information and informed consent will be done on the Internet-based platform in line with previous studies that we have conducted. Individuals who are 18 years or older with at least risky use of alcohol (≥6 p for women and ≥ 8 p for men) on the AUDIT included in the study. Furthermore, we will inform the participants that it is important that they intend to be available via the Internet for study within the next 10 weeks of the study. Persons under 18 and / or without risky use of alcohol are excluded. Persons who receive over 15 on the estimates of anxiety and depression the HADS, those who get a result that is two standard deviations or more below average in any of the instruments that measure quality of life (WHOQOL-BREF and the EQ-5D) may participate in the study but are recommended after 10 weeks to seek psychiatric help. Participants at the end of the study, scoring higher than 20 on the AUDIT will receive a recommendation to turn to specialized addiction treatment or addiction treatment provided by social services. Participants who, according to the Drug Use Disorders Identification Test (DUDIT), have an active drug use in parallel with the use of alcohol will be allowed to participate in the study, but if continuing drug use at the end of the study, they will receive a recommendation to above apply to the specialized addiction care or social services to continue help. Personal advice on this can be given if the person contacts the research team. Contact details will be available when logging on the personal user account, the treatment site. We expect that a smaller proportion of participants in the study will show signs of problematic drug use in parallel with problematic alcohol use. One population survey of drug problems from 2008, where DUDIT questionnaire was used, shows that the risk of drug consumption in 2% of the Swedish population and the harmful use of 2.8% (Sinadinovic et al., 2011).

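### As written, the screening procedure tells an under-18 whose AUDIT score meets the cut-off that no hazardous drinking was found

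*Protocol*

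**What the plan says.** Under Procedure, Recruitment, an interested person reads the consent information and must then "specify gender and age, and fill in the AUDIT - form". Two branches follow.

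- The failing branch opens "If the inclusion criteria for age and / or hazardous use of alcohol is not met". Its consequence is that "the individual will be informed that the hazardous use of alcohol is not present in the answers". The message then gives its conclusion: "he / she therefore does not belong to the target group of the study". Annex 4.1.1.1 is cited for this message.
- In the passing branch, the person is told that the criteria are met and creates a user account.

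The Participants section treats the two criteria as distinct grounds: "Persons under 18 and / or without risky use of alcohol are excluded". It sets risky use at an AUDIT score of at least 6 for women and at least 8 for men. The AUDIT description under Materials gives the same limits, "for men at 8 points or more, for women at 6 points or more", without restricting them by age, on an instrument "with a final score between 0 and 40".

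**The concern.** The failing branch is triggered by age or by drinking, but its message and its stated reason concern drinking only. No separate message for failure on age is described. A person under 18 with a score at or above the cut-off would therefore be told something that contradicts the questionnaire just completed, and would be given the wrong reason for being turned away.

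What is at stake is the accuracy of health information, not the trial's inference. The person has answered an advertisement about treatment for alcohol problems and would receive false reassurance. The protocol makes the research team's contact details available on logging in to the user account, and only those who meet the criteria create one, so the described route to personal advice does not clearly reach this person. The consent annex, which is not available here, may give contact details.

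**Working it through.** No sample size, power or error rate is involved. The check lists every combination of the two criteria and compares the described message with the eligibility rule.

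**Inputs**
- Age limit of 18 (Participants).
- AUDIT cut-off of 6 for women and 8 for men (Participants; the same limits under Materials).
- AUDIT range 0 to 40 (Materials).
- One message for all screen failures, saying that hazardous use is absent (Procedure, Recruitment).
- Age and AUDIT are both known before the message is issued (Procedure, Recruitment).

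**Combinations: 2 age groups × 2 AUDIT groups = 4**

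| Age | AUDIT | Outcome | Statement on drinking | Reason given |
|---|---|---|---|---|
| 18 or over | at or above cut-off | eligible | not issued | not issued |
| 18 or over | below cut-off | screened out | true | correct |
| under 18 | below cut-off | screened out | true | incomplete: age not named |
| under 18 | at or above cut-off | screened out | **false** | **wrong: age is the only ground** |

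Three combinations are screened out. The statement is true in two and false in one.

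**Could the last row go elsewhere?** The passing branch requires the inclusion criteria to be met, and a person under 18 does not meet them. The failing branch names age in its trigger. That row therefore falls in the failing branch, and no third branch is described.

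**Scores covered by the last row**
- Women: 6 to 40, that is 40 − 6 + 1 = 35 of the 41 possible scores.
- Men: 8 to 40, that is 40 − 8 + 1 = 33 of the 41 possible scores.
- Scores of 21 to 40, that is 40 − 21 + 1 = 20 values, are included for both.

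These are counts of possible scores, not of people. They show only that the false statement is not confined to borderline results: as described, it would be issued at any score from the cut-off to the maximum. For scale, the Participants section says that enrolled participants "scoring higher than 20 on the AUDIT will receive a recommendation to turn to specialized addiction treatment" if they do so at the end of the study. That rule does not apply to people screened out; it shows only how the protocol regards scores of that size.

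**The case against.** The strongest objection is that the sentence only paraphrases the message. The wording is in Annex 4.1.1.1, which is not available and may deal with age separately. The English also reads as a machine translation, and the point depends on the scope of a conjunction and of a single connecting word meaning 'for that reason'. The author may have compressed two rejection grounds into one sentence and spelled out only the commoner message. This stands as a limit: the protocol text alone does not show that any minor would in fact receive the false statement. It does not clear the sentence, which as written directs the wrong message and cites a single annex item for both kinds of failure. The same either-or-both construction appears in the exclusion rule under Participants, so it is not an isolated slip.

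It can also be said that the cut-offs were meant for adults. The eligibility sentence does concern adults, but Materials gives the limits without an age restriction and the protocol offers no other threshold for minors. If the cut-offs did not apply to minors, the protocol would have no basis for telling one that hazardous use is absent.

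Finally, few people are likely to be affected and nothing in the trial changes. Both are correct. The first recruitment route is an advertisement on one alcohol help site, with wider internet advertising only if recruitment is slow. Nobody affected creates an account or is randomised, and no ineligible person is let in. This limits the weight of the point but does not make the sentence right.

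**Conclusion.** The concern holds for the procedure as the protocol describes it. In one of the three screen-out combinations, under 18 with an AUDIT score at or above 6 (women) or 8 (men), the person is told something false about their drinking and given the wrong reason for exclusion. No other part of the protocol removes the contradiction.

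The point is minor. Randomisation, the planned 80 participants and the analysis are unaffected, and the number of people concerned cannot be derived from the document. The conclusion rests on two assumptions: that the annex and the screening software follow the sentence as written, and that the AUDIT cut-offs, stated without an age limit under Materials, are the protocol's standard for hazardous use at any age. Confidence is moderate because the annex is not available and the text appears to be translated.

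**What to change.** In Procedure, Recruitment, and in Annex 4.1.1.1:

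1. Issue the message that hazardous use was not found only when the AUDIT score is below 6 (women) or below 8 (men).
2. Give anyone under 18 a separate message that states age as the reason and does not contradict their AUDIT score. For a person under 18 who also scores below the cut-off, name age as a ground as well.
3. If the annex already separates the two cases, correct only the sentence in the protocol.

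Whether minors should also be directed to other help is for the responsible clinicians to decide.

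The cost is one extra message text and one condition on fields already collected (age, gender, AUDIT). Design, sample size and analysis do not change.

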**Statistics**

The results will be reported in anonymised form and statistical group level. Descriptive statistics for study participants' properties based on battery of questions will be presented, as well as analyses of the differences between the groups in the outcome. The primary measure of alcohol consumption is the AUDIT-C and TLFB. Secondary measures are other issues relating to anxiety, depression and quality of life. The analyses will be checked for motivation for treatment (Annex 5.4), other treatment during the study (treatment issues, Annex 5.10). Otherwise, additional results of the working alliance (Annex 5.8) and the platform's usability (Annex 5.9) will be presented.

This study is a pilot study in which the primary objective is to generate information and knowledge about various forms of Internet mediated therapist support. Since this is a pilot study we expect information about the feasibility and direction of outcomes (probably no significant differences). This is the first time that internet treatment with therapist support is tested in Sweden and the launch fits well with the National Board of Health guidance on disease prevention, where web-based treatment for problematic alcohol use is highlighted as an evidence-based action and which emphasizes that care must be equitable and accessible to all (National Board of Health, 2012).

National Board guidelines further states that care should be constructed as a so-called *stepped Care* model where light interventions are considered first, followed by more extensive if the first intervention would not have the desired effect. Today there are first steps in such a model by eScreen.se (Sinadinovic, 2012) and Alkoholhjalpen.se (Sinadinovic et al., 2012) and the Alcohol Line ([name], personal communication, 2012). Internet treatment is needed to provide a further step in the model, when the self-screening (eScreen.se) or work with self-help (alkoholhjalpen.se) or telephone (Alcohol line) does not lead to reduced or eliminated drinking. The increased accessibility to treatment via the Internet could potentially treatment more accessible to people who live in rural areas. Since only 20% of people with alcohol dependence seek help through addiction services Internet-based treatment could also reach the large proportion of people regardless of residence do not seek help, possibly because of the risk of stigmatization (Blomqvist et al., 2007). Internet based treatment with therapist support is in the current only an option for a few psychiatric diagnoses, but when it comes to substance abuse problems, there is no such option yet. This study is an important step in making such treatment available in Sweden.

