To date, treatment for problematic alcohol use over the internet has been tested in Sweden only in self help format (without therapist support), where help seekers on the internet were randomly assigned to eScreen.se (screening site), alkoholhjalpen.se (self-help modules) or a control group that completed questionnaires; follow-up was done after 3, 6 and 12 months (Sinadinovic, Wennberg, Johansson, & Berman, 2012). Alkoholhjälpen.se yielded better effect for those who had a little less severe problems. Of those who used eScreen.se 70% went on to talk to someone about their problems, compared with 49% from Alkoholhjälpen and 56% for the control group. These results are consistent with the overall positive results of the studies included in the review articles and meta-analyzes (Newman, Szkodny, Llera, & Przeworski, 2010; Rooke, Thorsteinsson, Karpin, Copeland, & Allsop, 2010).

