3. The study published by Blankers et al. (2011) consisted of three arms: TO with therapist support in the form of seven 40-minute chat sessions in real time, TO without therapist support and a control group in the form of a waiting list. In this pilot study, we want to partially replicate Blankers et al. study and compare treatment outcomes for TO with therapist support, with the outcome of the TO without therapist support. In order to answer this question 40 individuals will be randomized into ***group 3 to receive*** TO without therapist support. Answering this question will be generated after the data analyzes where groups 1 and 2 will be compared with group 3.

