SRS (Session Rating Scale) (Appendix 5.8.1 for group 1 & 2 and 5.8.2 for Group 3) is a tool to measure the alliance. It can be administered after each session or module. It is a short test where the respondent is asked to consider the extent to which he or she agrees with four different statements; *"I* felt *heard, understood and respected." "We worked with or talked about it that I wanted to work with and talk about."* " *The way we worked in suits me fine.* "And" *Today's talks suited me perfectly.* ". Grading is done on a VAS-scale (Visual Analogue Scale) with the above statements on the one hand and the claims formulated as negatives of the other. SRS is clearly analogous to the longer test designed to measure the same thing, both in terms of validity and reliability (Campbell & Hemsley, 2009).

Follow-up questions (Appendix 5.9.1 Group 1 & 2 and 5.9.2 of Group 3) will investigate how participants experienced the Internet treatment; if they missed having telephone or physical contact, if they experienced the treatment as effective and whether they would recommend the treatment to anyone. The answers are sometimes graded, sometimes formulated as "Yes," no "and" do not know " (Postel et al, 2011).

  Other forms of treatment (Appendix 5.10)  This short questionnaire developed by the research group contains three questions relating to whether the participant used other measures of help besides the Internet treatment to manage his or her problem, including questions about medication and whether the person had contact with other responders - both self-help, telephone or customary care. By controlling for other factors, it becomes easier to assess the impact of the completed treatment (Sinadinovic et al, 2012; Sinadinovic, Johansson, Wennberg, & Berman, 2010).

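### Adjusting the arm comparison for other treatment used during the study can bias the estimated effect of assignment, because that variable is measured after randomisation and therapist contact could change it

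*Protocol*

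**What the plan says.** The Statistics section announces analyses of group differences in outcome and names the main drinking measures: "The primary measure of alcohol consumption is the AUDIT-C and TLFB". It then says: "The analyses will be checked for motivation for treatment (Annex 5.4), other treatment during the study (treatment issues, Annex 5.10"). It names no unadjusted analysis as the main one, and it does not call the adjustment a sensitivity or mediation analysis.

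The wording of that sentence is loose, but the Materials section, under Other forms of treatment, makes the intent clear. The Annex 5.10 form asks "whether the participant used other measures of help besides the Internet treatment to manage his or her problem", including medication, self-help, telephone and ordinary care. The stated reason for collecting it is: "By controlling for other factors, it becomes easier to assess the impact of the completed treatment".

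The Procedure section (Recruitment) fixes the timing: "After completion of treatment, participants fill in outcome measurements again and processing issues and follow-up questions (Annexes 5.1-5.10").

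The comparison concerned is question 3 in the Purpose section, where "groups 1 and 2 will be compared with group 3": 20 + 20 participants with therapist support against 40 without.

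**The concern.** Randomisation makes the arms comparable on everything fixed before assignment. It gives no such protection within levels of something that happens afterwards. Outside help during the 10 weeks is of that kind. A participant working alone may look for help elsewhere, while one with weekly therapist contact may need less of it or may be encouraged to seek more. The Procedure section (Treatment) also offers participants whose mood worsens considerably a contact about suitable health care, so outside care can partly reflect how someone fares on the assigned programme.

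If assignment changes outside help, adjusting for it can distort the arm difference in two ways:

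- **Mediation.** Any effect on drinking that runs through outside help is removed from the estimate.
- **Confounding within levels of help.** If an unmeasured factor such as severity drives both help-seeking and drinking, users of outside help in one arm are no longer comparable with users in the other.

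The Statistics section expects the pilot to show the direction of outcomes rather than significance. Direction is what such an adjustment could disturb. For a variable of this kind, the rationale in Materials does not hold for the effect of assignment.

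**Working it through.** The protocol states no figure on this point, so there is nothing to reproduce. The check has two parts.

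**1. Does the protocol fix a post-randomisation covariate?** Three places, read together:

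- Statistics: the adjustment variable is other treatment during the study.
- Materials: the form records help used alongside the internet treatment, and the purpose is control.
- Procedure: the form is completed after treatment, together with the outcomes.

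The answer is yes. The variable cannot be a baseline value.

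**2. How large could the distortion be?** Let Y be drinking in SD units (lower is better), T the arm (1 = therapist support) and H use of other help (yes/no), with proportions p1 and p0 in the two arms. For least squares, an exact identity holds:

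adjusted − unadjusted arm difference = −b × (p1 − p0),

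where b is the coefficient of H in the adjusted model. Suppose other help lowers drinking by η, and unmeasured severity (SD 1) has loading λ on drinking. Then b = −η + λk, where k is the within-arm difference in mean severity between users and non-users of other help.

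*Inputs.* The proportions 70%, 49% and 56% are borrowed from the Background section. Everything else is assumed: η from 0 to 0.4, λ from 0 to 0.6, and severity raising the log-odds of seeking help by 0 to 1.5 per SD. Numerical integration of the logistic model at 70% versus 49% gives k = 1.074 at log-odds 1.5 and k = 0.671 at 0.75.

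*Results at 70% versus 49%* (p1 − p0 = 0.21):

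| Case | b | Shift (SD) |
|---|---|---|
| Mediation only: η = 0.4, λ = 0 | −0.400 | +0.084 |
| Confounding only, maximal: η = 0, λ = 0.6, log-odds 1.5 | 0.6 × 1.074 = 0.644 | −0.135 |
| Both at maximum | −0.4 + 0.644 = 0.244 | −0.051 |
| Mid-range: η = 0.2, λ = 0.3, log-odds 0.75 | −0.2 + 0.3 × 0.671 ≈ 0.001 | 0.000 |

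Swapping the rates (49% versus 70%) reverses every sign, so the extreme is about 0.13 SD in either direction. With 56% versus 49% (p1 − p0 = 0.07), the range is about −0.045 to +0.028 SD. With equal use in both arms, the shift is 0 whatever the other inputs.

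*A second model* used a probit form with an assumed direct effect of −0.3 SD, again at 70% versus 49%. Mediation alone (η = 0.3) moved the estimate from −0.363 to −0.301, a shift of +0.062 (by the identity, 0.3 × 0.21 = 0.063). Confounding alone (λ = 0.5, probit loading 0.5) moved it from −0.299 to −0.376, a shift of about −0.08, or roughly a quarter of the effect. With both present the shift was −0.013.

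*For scale:* the standard error of the 40 versus 40 difference is √(1/40 + 1/40) = 0.22 SD with complete data.

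**The case against.** The strongest objection is that the bias is conditional and small. It arises only if assignment changes outside help and that help affects drinking or shares causes with it. Even the extreme case is below the sampling error of the comparison, and it requires other help to have no effect on drinking while confounding is at its maximum. This stands, and it limits the claim to *can be biased*.

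A reader might infer from the Background section that the effect of assignment on outside help is already shown, since in an earlier Swedish randomised study of internet self-help "70% went on to talk to someone about their problems, compared with 49% from Alkoholhjälpen and 56% for the control group". The text does not support that. The figures come without sample sizes or intervals, and the first is for those who used the screening site, who may not be everyone randomised to it. The programmes had no therapist support. Talking to someone is not what Annex 5.10 measures, and follow-up was at 3, 6 and 12 months rather than 10 weeks. The figures show only a conceivable spread.

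It could also be said that a statistical analysis plan may settle the model. But the protocol itself names the variable and gives the reason for adjusting, so this is more than a detail left open.

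Other extensions do not hold:

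- **Irreversible harm.** An unadjusted comparison uses the same data and can be run at any time, although choosing it after seeing results is weaker than naming it in advance.
- **Extra missing data.** Annex 5.10 is collected with the outcomes, so a participant without the form will mostly lack the outcome too.
- **Motivation (Annex 5.4).** It is measured at recruitment as well as at the end, and the protocol does not say that the later value is the covariate. That is unspecified detail, not a stated error.

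**Conclusion.** The point holds in a limited form. The protocol fixes adjustment of the between-arm outcome analyses for a variable that is reported after treatment and that therapist contact could plausibly change. The adjusted contrast of groups 1 and 2 with group 3 can therefore be biased for the effect of assignment, and neither the size nor the direction can be determined from the protocol.

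The sizes above are illustrations that rest on borrowed rates and on assumed effects of help and severity. A reader might infer that the adjusted estimate is certain to be wrong, or that the pilot is compromised. Neither follows: the study has 80 participants, expects probably no significant differences, attaches no decision rule to the adjusted estimate and leaves confirmation to a later powered trial. Severity: should be fixed.

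**What to change.** - In Statistics, state that the main comparison of groups 1 and 2 with group 3 does not adjust for other treatment during the study, and that any covariates are baseline (T1) values. If motivation is kept, this means its T1 value.
- Report the Annex 5.10 answers by arm, as a result in their own right.
- Label any analysis adjusted for other treatment as exploratory and state its assumptions. It need not be dropped altogether.
- In Materials, replace the rationale for the form: it describes outside help by arm and helps interpretation, but controlling for it does not isolate the effect of assignment.

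The cost is a few sentences of text and a little extra reporting, with no new data or participants. The main comparison then estimates the effect of assignment including any outside help it prompts or replaces, and it is free of the bias described here.
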